## Abstract

Stroke often affects arm functions and thus impairs patients' daily activities. Recently, several studies have shown that additional movement acoustics can enhance motor perception and motor control. Therefore, a new method has been developed that allows providing auditory feedback about arm movement trajectories in real-time for motor rehabilitation after stroke. The present article describes the study protocol for a randomized, controlled, examiner, and patient blinded superiority trial (German Clinical Trials Register, www.drks.de, DRKS00011419), in which the method will be applied to 13 subacute stroke patients with hemiparesis during 12 sessions of 30 min each as additional feedback during the regular movement therapy. As primary outcome, a significant pre-post-change in the Box and Block Test is expected that exceeds the performance increase of 13 patients who will be provided with sham-acoustics. Possible limitations of the method as well as the study design are discussed.

## Introduction

### Background

Stroke is the second most common cause of death among the neurological disorders. The great majority of patients who survive a stroke have to rely on health care support afterwards (1). Sensory and motor impairments can lead to dramatic limitations of everyday motor skills and temporary or permanent disability. Most often arm functions are impaired and hamper patients during activities of daily living (2). Hemiparesis, for example, affects spatial and temporal arm motor control and results in disturbed movement trajectories, lower movement amplitudes and enhanced movement times (3). Therefore, one important goal of motor rehabilitation is the improvement of arm functions. Some therapies like the Arm Ability Training (4) or the Constraint Induced Movement Therapy (5) predominantly focus on the improvement of the motor components of the arm movement system. However, Bastian points out that efficacy of stroke rehabilitation might be improved by methods that combine perceptual- and motor oriented approaches (6). A recent study with healthy participants showed a higher efficacy of a sensorimotor compared to a purely motor orientated approach, accordingly, although both approaches address the same adaptation mechanisms (7). An example for a perception-oriented approach for stroke rehabilitation is Ramachandran's mirror visual feedback method. It seems to reestablish congruency between motor commands and visual feedback in patients that watch a mirror image of the unimpaired arm during bilateral movements. Some of these patients report not only to see the impaired arm, but also to feel it moving. A probable explanation is that mirror visual feedback revives temporarily inactive motor neurons and/or ipsilateral corticospinal pathways (8).

As alternative to vision-oriented approaches, a specific feature of recently developed methods is the implementation of auditory signals and sounds to generate additional perceptual information about movement quantities and qualities (9, 10). In particular, music has been shown to be an efficient add-on in stroke therapy: Schneider et al. (11) showed that a music based arm therapy can outperform highly established approaches like the constraint induced movement therapy. Chen et al. (12) reported from a proof of concept case study on five stroke patients that rhythmic auditory cueing enhanced movement speed. Furthermore, two-state continuous musical feedback increased elbow extension as well as shoulder flexion and reduced compensatory trunk movements. Growing evidence suggests that music-supported therapy is superior to conventional physiotherapy without music, probably because it acts on multiple levels and addresses motor, cognitive, and emotional mechanisms (13).

Furthermore, some studies indicate beneficial effects of continuous auditory feedback for movement rehabilitation after stroke. For example, Maulucci and Eckhouse (14) reported that stroke patients relearned functional movement paths faster when they were provided with auditory feedback about spatial deviations from reach paths performed by healthy persons. Secoli et al. (15) found that auditory feedback improved performance in a movement tracking task performed during robot-assisted arm training in patients with chronic left hemiparesis. However, other results were equivocal: According to Robertson et al. (16), feedback about hand orientation during reaching seems to be beneficial for patients with right hemisphere lesions, but detrimental for patients with left hemisphere lesions. Based on a systematic literature review, Molier and colleagues see a possible benefit of performance feedback and augmented auditory feedback, although the determinants for their efficacy remain largely unknown (17).

Since stroke often impairs somatosensation (18, 19), recovery of arm functions might benefit from methods that support proprioception, particularly. Hereto, Sihvonen et al. (13) argue that music-supported therapy might be effective, again, because patients generate an internal expectation about when the next note is going to be heard and thereby improve their movement timing. However, by considering proprioception as integrated percept of multiple sensory streams from multiple receptors which is experienced as motion and position sense, further methods might address specific proprioceptive mechanisms and thereby support the relearning of functional movement patterns after stroke. The method of movement sonification might have this potential. Movement sonification represents a concept for mapping movement parameters to sound in order to create novel perceptual streams congruent to the time course of kinematic or dynamic movement parameters (20). This method differs conceptually from providing feedback on performance errors, because it allows to design artificial perceptual streams structurally equivalent to perceptual streams from other modalities. It has been shown that the amendment of visual motion information by movement acoustics amplifies the activity of multimodal integration areas in the brains of observers and furthermore, activates the basal-ganglia-fronto-cortical motor loop (21, 22). Accordingly, movement sonification has been shown to support learning (23, 24) and adaptation (25) of fine motor skills, (re)learning of arm joint coordination patterns (26) and acquisition of gross motor skills (27, 28) in healthy persons. In deafferented patients, it can substitute proprioception (29). Studies on immediate effects of movement sonification on movement pattern recognition, movement synchronization and own-other discrimination (30–33) indicate that movement sonification unfolds its potentials on perception and action by linking to internal movement representations.

### Theoretical approach

The present approach is based on a further development of a method presented in Vinken et al. (31) and Schmitz et al. (34). It differs from other approaches as it focuses on sensorimotor representations of hand and arm movements as suggested by Bastian (6) for arm training in stroke rehabilitation. Studies indicate that hand and arm movements are represented in body-centered reference frames and that arm trajectories are realized on the basis of muscle synergies (35–38). Findings from Overduin and colleagues indicate that muscle synergies are represented in the brain in a time-invariant spatial as well as a time-varying spatiotemporal manner (39). d'Avella et al. (40) showed that different muscle synergies are active during movements to different directions, but a few synergies can sufficiently explain coordinated muscular activity during movements with different amplitudes, loads, forearm postures, as well as movement sequences. Such results indicate that synergies serve the implementation of a few global movement features like movement direction and amplitude which are coded by independent neuronal populations in the brain (35). Accordingly, it seems to be reasonable to design feedback related to movement direction and amplitude in an egocentric reference frame to address arm movement control and muscle synergies. Since stroke seems to disrupt muscle synergy patterns of the impaired arm (41), significant effects of such feedback might be expected for the rehabilitation of arm functions. Moreover, muscle synergy patterns are highly correlated between arms and the reorganization of muscle synergy patterns is part of the recovery process after stroke (41). By providing homogenous feedback on movements of each arm, the unimpaired arm can serve as individualized movement model as well as auditory mirror image and might support the reorganization process.

The goal of the intended clinical trial is to prove the impact of a novel method for arm movement sonification in motor rehabilitation after stroke. The method provides real-time feedback about three-dimensional wrist movements in relation to the trunk. Auditory feedback informs about the angular direction of movements in the horizontal and vertical plane, the radial amplitude as well as the absolute velocity of the wrist. Accordingly, each movement produces an unequivocal sound which represents additional sensory feedback. We hypothesize that patients benefit from the real time feedback during movements with the impaired arm due to the structural equivalence of the sound to movement information from other modalities which can amplify activity of multisensory integration areas in the brain, support motor control and substitute partially lost proprioception as indicated by Scheef et al. (21), Schmitz et al. (22), Effenberg et al. (28) and Danna and Velay (29). A pilot study with a precursor version of this method provided encouraging results as four stroke patients showed improved performance in the Box and Block test after five training sessions (34). Furthermore, a related method has recently been applied in a randomized controlled clinical trial by Scholz et al. (42). After an exploration-phase, stroke patients learned to play simple melodies by moving their impaired arm in 3D-Cartesian space. Ten training sessions of 20 min each with this musical sonification reduced pain according to the pain-score of the Fugl-Meyer test, enhanced hand functions as assessed by the Stroke Impact Scale and increased smoothness of reaching as shown by kinematic analyses. Effect sizes were moderate. The present approach differs from the method presented in Scholz et al. (42) mainly by the way arm movements are sonified and by capturing the whole upper body. This allows providing intuitive feedback for both arms while controlling for upper body movements. Thus, the present method prospects even larger effects.

### Objectives

The primary objective of this trial is to investigate the effectiveness of the above mentioned approach for real-time movement sonification on motor abilities of the paretic upper limb in subacute stroke patients. The hypotheses are that, compared to patients provided with an auditory control stimulus, patients provided with real-time movement sonification (1) improve gross motor dexterity of the paretic upper limb assessed with the Box and Block test, and (2) motor function of the paretic arm and hand measured with the Action Research Arm Test and the Stroke Upper Limbs Capacity Scale.

### Trial design

The present trial is designed as a randomized, controlled, assessor and patient blinded superiority trial with two parallel groups. Randomization is performed as block randomization with 1:1 allocation.

## Methods

### Study setting and eligibility criteria

All subjects included in the study are inpatients at a rehabilitation hospital in Germany. They meet the following inclusion criteria: hemiparesis of the upper extremity (SULCS score ≥3) after a unilateral ischemic or hemorrhagic stroke (4 weeks to 6 months after stroke onset), the functional ability to pick up a wooden cube (2.5 cm in size) with the paretic hand, and age between 18 and 80 years. Patients with unstable fracture, the inability to sit for 30 min, or severe aphasia or cognitive impairment, which compromises the implementation of the assessments or the therapy are excluded from the trial.

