### Outcomes

Primary outcome measure is the Box and Block Test (44). The test is a measure of unilateral gross manual dexterity. It counts the number of wooden blocks that can be transported from one compartment of a box to another compartment within 1 min. The Box and Block test shows high test-retest and interrater reliabilities in elderly subjects and subjects with neurological disorders (45, 46). The construct validity of the test is high when compared with the ARAT and the Fugl-Meyer test (45, 46). The Box and Block test is suitable to detect changes over time in stroke patients (47).

Secondary outcome measures are the Action Research Arm Test (ARAT) and the Stroke Upper Limbs Capacity Scale (SULCS). The ARAT assesses mainly the ability to handle smaller and larger objects with a variety of qualitatively rated items. It includes four subtests: grasp (6 items), grip (4 items), pinch (6 items), and gross movement (3 items). The scores for each item range from 0 to 3. We use the standardized protocol published by Yozbatiran et al. (48) to assess the ARAT. The test shows high intrarater reliability and interrater reliability. Validity is high when compared to the Fugl-Meyer test and it is sensitive to detect changes (47).

The SULCS assesses the capacity of the paretic upper limb in stroke patients. It consists of 10 items which represent tasks that are related to daily activities (49). The items assess proximal arm capacity without need for active wrist or finger movement (3 items), arm capacity combined with basic hand capacity (grasp tasks without manipulating, 4 items), and advanced hand capacity (manipulating tasks, 3 items). The scale has good interrater reliability and a high construct validity when compared with the ARAT and the Rivermead Motor Assessment (RMA) (50).

All these outcome measures are assessed at baseline before the start of the intervention, at post-test after the last intervention, and at follow-up test 2 weeks after the end of the intervention. The measures are assessed by an assessor blind to treatment allocation. The assessor is experienced and trained in performing the clinical assessments.

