### Allocation

Patients included in the study are randomly assigned to either the control or the experimental group with a 1:1 allocation as per a computer generated randomization schedule stratified by age (<60 and ≥60 years) and lesion side (left and right sided) using blocks of random sizes. The block sizes will not be disclosed to ensure concealment. The randomization schedule will be concealed until the primary endpoint will be analyzed. The allocation is done by a scientific staff member not directly involved in the project. The staff member sends a form with the allocated intervention to the therapist who is not involved in assessing the outcome measures.

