### Statistical methods

Descriptive statistics including means and standard deviations or medians and 25th and 75th percentiles for continuous data, and frequencies for categorical data will be determined. The appropriateness of the randomization will be examined by testing for between group differences in demographical and clinical variables (e.g., age, time since stroke, SULCS score).

Among the cases available for analyses, intention-to-treat analyses will be performed. For all outcome measures, the within-subject differences between the baseline and post-test, and the baseline and follow-up test are of central interest in the intervention group compared to the control group. For the primary outcome measure, a repeated measures analysis of variance will be used. Pairwise comparisons will be generated using Tukey's method. A subgroup analysis will be performed to investigate the influence of lesion side. For the secondary ordinal outcome measures, non-parametric statistics will be used. Between-group comparisons (intervention vs. control group) will be performed to compare the short-term changes (baseline—post-test) and long-term changes (baseline—follow-up) between groups using Mann-Whitney *U*-tests. In addition within-group comparisons will be performed using Friedman tests. If the Friedman test showed significant differences, Wilcoxon matched-pairs tests will be used to compare baseline and post, and baseline and follow-up measures. Effect sizes (r) of changes between groups and within-groups will be calculated.

In addition, a per protocol analysis will be done, excluding patients who deviated from the protocol. Missing data will be replaced by the last value carried forward method.

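### The primary Box and Block model leaves out time since stroke, although eligibility runs from 4 weeks to 6 months; adding it as one pre-specified covariate is a cheap, optional gain in precision

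*Protocol article*

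**What the plan says.** Under Study setting and eligibility criteria, the article admits patients "4 weeks to 6 months after stroke onset". The outcome is measured three times: before treatment starts, once it has finished, and again 2 weeks later (Outcomes).

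Under Statistical methods, the quantity of interest is change, set against the sham arm: "the within-subject differences between the baseline and post-test, and the baseline and follow-up test are of central interest in the intervention group compared to the" […]. The model is named in the same section: "For the primary outcome measure, a repeated measures analysis of variance will be used". No covariate is listed, and the only subgroup analysis concerns lesion side.

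Time since stroke appears once in the analysis, where randomisation is to be checked by "testing for between group differences in demographical and clinical variables (e.g., age, time since stroke, SULCS score"). The text does not say what follows if the groups differ. Under Allocation, the schedule is "stratified by age (<60 and ≥60 years) and lesion side (left and right sided) using blocks of random sizes", so time since stroke is not a stratum.

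Under Sample size, the inputs are f = 0.2, a correlation of 0.7 among repeated measures, 80% power and α = 0.05, giving 26 patients in total.

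**The concern.** All patients continue the hospital's normal therapy during the study (Interventions), so a patient's change in blocks contains background recovery as well as any effect of sonification. The window allows one patient to enter at week 4 and another at about week 26. If background recovery over the following 3 to 5 weeks differs between such patients, the difference is a source of spread in the primary change score.

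The within-subject design does not remove it. Comparing each patient with his or her own baseline takes out stable differences in level, but not differences in rate of change. Only a term that acts on the change, which means the covariate crossed with visit, would take it out.

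What is at stake is precision in a trial of 13 patients per arm, using a variable the sponsor already records and already considers worth checking at baseline.

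**Working it through.** **1. Reproduce the plan's figure.** The calculation uses the noncentral F test for the group-by-visit interaction, with k = 2 groups, m visits and N = 26:

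- λ = f²·N·m / (1 − ρ), df1 = (k − 1)(m − 1), df2 = (N − k)(m − 1).
- Three visits: λ = 0.04 × 26 × 3 / 0.3 = 10.4 on 2 and 48 df. Power is 80.6%, and N = 26 is the smallest even total reaching 80%. The stated sample size is reproduced.
- Two visits (baseline to post only): λ = 0.04 × 26 × 2 / 0.3 = 6.93 on 1 and 24 df. Power is 71.5%.

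The gap between 80.6% and 71.5% comes from testing three visits rather than two. It has nothing to do with time since stroke.

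**2. Add the covariate.** Let R² be the share of the variance of change that time since stroke explains. The documents give no value, so R² is an assumption, shown from 0% to 30%. The calculation takes the stated 0.7 to be the correlation before any adjustment. Adjustment then multiplies the error variance by (1 − R²), so λ is divided by (1 − R²). One covariate is charged: df2 falls from 48 to 46 for three visits (its interaction with visit takes 2) and from 24 to 23 for two.

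| Assumed R² | λ, three visits | Power, three visits | λ, two visits | Power, baseline to post |
|---|---|---|---|---|
| Unadjusted plan | 10.40 | 80.6% | 6.93 | 71.5% |
| 0% | 10.40 | 80.4% | 6.93 | 71.3% |
| 5% | 10.95 | 82.5% | 7.30 | 73.5% |
| 10% | 11.56 | 84.6% | 7.70 | 75.7% |
| 20% | 13.00 | 88.8% | 8.67 | 80.5% |
| 30% | 14.86 | 92.6% | 9.90 | 85.4% |

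If the covariate proves useless, the loss is 0.2 percentage points.

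**3. Check validity without the covariate.** In 100,000 simulated trials with 13 per arm, no treatment effect and R² = 20%, the unadjusted two-sided 5% test on the change score rejected in 4.9%. Type I error is nominal.

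**4. Check whether the planned baseline test helps.** With 13 per arm, a two-sample t test has about 23% power against a true difference of 0.5 SD. A non-significant result would say little, and a significant one leads to no stated step.

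**The case against.** The strongest reply is that nothing here is wrong. Leaving a prognostic variable out of a randomised comparison biases nothing, and a condensed article may leave covariates to a fuller document. The first part stands in full. The second carries some weight, since the text does not exclude covariates. But the article does name the primary model, and the proposal is a specific improvement to that model rather than a request for missing detail.

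The reply also holds that no passage says recovery varies with time since stroke within this window, and that the eligible range need not be the enrolled spread in a single hospital's inpatients. That stands too. Both the premise and its size are assumptions, which is why the table starts at zero.

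A reader might infer four stronger things that the documents do not support:

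- **That the trial is underpowered for this reason.** The 0.7 is stated without any condition on time since stroke. If it already contains this variation, the planned three-visit test has its 80.6%, and adjustment adds to that rather than repairing a deficit. The 71.5% belongs to the two-visit contrast and is a separate matter.
- **That chance imbalance is a second problem on top of noise.** With 13 per arm, the difference in mean time since stroke has a standard error of √(2/13) = 0.39 SD, so a gap above 0.5 SD arises in about 20% of randomisations. At R² = 20% such a gap shifts the arm difference by 0.5 × √0.2 = 0.22 SD of change. That is 0.22/0.39, or about 0.57 of the standard error of the arm difference. It can fall either way and is already part of the sampling error the unadjusted test carries.
- **That time since stroke should have been a stratum.** Two factors already give four strata for about 32 enrolled patients, so a third factor would be impractical. A covariate achieves the aim without one.
- **That equal baseline scores early and late after stroke are known to predict different gains.** The documents do not say so.

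**Conclusion.** The point holds as an optional gain in precision. The stated primary model omits a variable that the trial collects and that may explain part of the spread in change, and the one use made of that variable leads nowhere. Validity is not in question.

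The gain depends entirely on the assumed R². On the three-visit test it ranges from a loss of 0.2 points at 0% to a gain of about 12 points at 30% (92.6% − 80.6%). On the baseline-to-post contrast it ranges from the same small loss to a gain of about 14 points (85.4% − 71.5%). These figures also rest on f = 0.2, on a correlation of 0.7 that already includes any effect of time since stroke, and on 26 analysed patients. The case for acting is that the possible loss is very small and no new data are needed.

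**What to change.** Before unblinding, add one sentence to the primary analysis: the Box and Block model includes time since stroke as a single continuous covariate, in one form fixed in advance (for example log weeks from onset to baseline), together with its interaction with visit so that it acts on the change. Fixing the form now avoids a choice made after seeing the data. Allocation already keeps the schedule concealed until the primary endpoint is analysed, so there is room to do this. Leave randomisation as it is.

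The cost is one or two error degrees of freedom and a slightly less simple model. There is no gain if recovery proves unrelated to time since stroke. If terms for baseline score or the two strata are also planned, the total number of terms should be kept small for 26 patients.
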